### Anthropometry

All anthropometry measures will be taken by qualified research nurses trained in anthropometry. Weight will be measured using a calibrated scale, standing height using a height scale, and mid-upper arm circumference (MUAC) using a MUAC tape. Grip strength will be measured using a Takei Grip-D dynamometer, waist and hip circumferences using a measuring tape, and lean and fat mass using a BodyStat
^®^ 1500 Impedance instrument (BodyStat
^®^, Douglas, Isle of Man).

### Dietary assessment

A multi-pass 24-hour dietary recall will be used to assess participants on day 2. All participants will be asked about the food they may have had in the last 24 hours which will be documented (Described in detail elsewhere.
^
36
^ While this 24-hour period may not be representative of the participants’ habitual intake, it was intended primarily to help interpretation of the metabolic profiling and thus would be most useful prior to the collection of samples for metabolic analysis.

## Clinical investigations: Zambia

Investigations will be carried out over a four-day period (shown in
Figure 2).

**Figure 2. f2:**
[figure not shown]
Study schema illustrating sample collection across the 4-day study period. Schema showing each sample collection time point throughout study, Day 1; No samples will be collected; Day 2; 9 mL heparinised blood; 2 mL EDTA blood; 5 mL citrated blood; 11 mL Urine at 00 and 180 mins; 4-8 g of stool; 0.5-2 mL of saliva at 00 and 180 mins; and breath samples every 20 mins. Day 3: 9 mL of heparinised blood; intermediate 2 mL heparinised blood samples every 20 mins for 1 h and every 30 mins for the last 2 h; breath samples every 20 mins; 0.5-2mL of saliva at 00, 60, 120 and 180 mins; 7 mL of urine at 00 and 180 mins; 4-8 g stool; 8 duodenal biopsies and 1 duodenal brushing; Day 4; 2-4 g of stool and 11 mL of urine.

### Day 1

This will include the final consent interview, administration of a questionnaire by the study nurse, clinical examination, and anthropometry (including weight, height, impedance, and deuterium approaches to body composition). Urine and stool collection devices will also be given.

### Day 2

Participants will bring urine and stool samples with them. Before administration of the solutions, a saliva sample, 9 mL of blood will be collected in lithium heparin, 2 mL in EDTA and 4.5 mL in citrated blood collection tubes, respectively, by venepuncture. A drink (prepared as shown in
Table 3) of
^2^H
_2_O (deuterated water, 1 g
^2^H
_2_O per kg body weight) containing
^13^C-spirulina protein (1.25 mg kg
^−1^) and (
^2^H
_8_)-Phe (0.035 mg kg
^−1^ in 200 mL clean water) will then be given at, or close to, 08:00 followed by breath sample collection using a straw and Exetainer tube (Labco, UK) every 20 mins for the first 1 h and every 30 mins for the remaining 3 h. A saliva sample will be collected at 180 mins, and a urine sample collection at 180 mins (3 h). A second drink of
^2^H
_2_O (1 g
^2^H
_2_O per kg body weight) will be given at 180 mins (3 h). During these procedures, a multi-pass 24-hour dietary recall will be administered by the study nurse. At the end of the procedures, the participant will be asked to fast after midnight and given stool and urine collection devices in readiness for day 3 procedures.

**Table 3. T3:** Composition of test solutions.

Solution	Composition	Administration
Solution A	• Deuterated water (D _2_O) (1 mL per kg body weight), • ^13^C-spirulina protein (1.25 mg kg ^−1^), and • ( ^2^H _8_)-Phe (200 mg) in 200 mL water	Oral, given at the beginning of day 2 procedures
Solution B	• Deuterated water (D _2_O) (1 mL per kg body weight)	Oral, given at the end of day 2 procedures
Solution C	• ^2^H _5_-Phe (0.6 μmol kg ^−1^), • 5,5,5- ^2^H _3_-Leu (1.2 μmol kg ^−1^) made up to 10 mL with sterile filtered normal saline	Day 3, given intravenously as slow bolus at beginning of procedures
Solution D	• ^2^H _5_-Phe (0.15 μmol kg ^−1^) • 5,5,5- ^2^H _3_-leucine (0.3 μmol kg ^−1^) made up to 20 mL in sterile filtered normal saline	Day 3, given intravenously as continuous infusion over 3 hours
Solution E	• ^13^C _6_-Phe (0.6 μmol kg ^−1^), • ^13^C _6_-Leu (1.2 μmol kg ^−1^), • 5 g lactulose, • 1 g rhamnose, • 0.5 g D-xylose, • 0.2 g 3-O-methyl D-glucose, • 200 mg sodium fluorescein, • 1.667 mg L-arginine-(guanidineimino- ^15^N _2_) HCl, • 1.0 g glycyl sarcosine in 200 mL water	Day 3, given orally as bolus at beginning of procedures
Solution F	• ^13^C _6_-Phe (0.15 μmol kg ^−1^) • ^13^C _6_-Leu (0.3 μmol kg ^−1^) made up to 600 mL in clean water	Day 3, given orally as sips every 20 mins

### Day 3

Following an overnight fast, an intravenous cannula will be introduced into both arms and 5 mL of blood will be collected into a lithium heparin tube via cannula. The fingertip probe will be clamped gently onto a fingertip, and continuous fluorescence recordings will begin. An intravenous bolus of
^2^H
_5_-phenylalanine (0.6 mmol kg
^−1^) and 5,5,5-
^2^H
_3_-leucine (1.2 mmol kg
^−1^) in 10 mL normal saline filtered through a 0.2 mm syringe filter (solution C) will be given over 2 mins, and an oral bolus of
^13^C
_6_-leucine (1.2 mmol kg
^−1^),
^13^C
_6_-phenylalanine (0.6 mmol kg
^−1^), 5 g lactulose, 1 g rhamnose, 0.5 g D-xylose, 0.2 g 3-O methyl-D-glucose, 200 mg fluorescein, 1.667 mg L-arginine-(guanidineimino-
^15^N
_2_) HCl and 1.0 g glycyl sarcosine (solution E) given. A continuous intravenous infusion of
^2^H
_5_-phenylalanine (0.15 mmol kg
^−1^) and
^2^H
_3_-leucine (0.3 mmol kg
^−1^) (solution D) will be commenced, at 5 mL h
^−1^, and sips of
^13^C
_6_-phenylalanine (0.15 mmol kg
^−1^) and
^13^C
_6_-leucine (0.3 mmol kg
^−1^) (solution F) administered as sips every 20 mins (prepared as shown in
Table 3). Breath samples will be collected every 20 mins for the first 1 h and every 30 mins for the remaining 3 h. Blood samples will be collected into lithium heparin collection tubes via the intravenous cannula: 2 mL every 20 mins for the first 1 h and every 30 mins for the remaining 3 h, and 5mL for the last sample. Urine will be collected up to 180 mins (3 h) while saliva collected every 60 mins for 3 h. After 240 mins (4 h) the participant will be transferred to the endoscopy room where upper gastrointestinal endoscopy will be performed using doses of sedation with midazolam and pethidine selected by the endoscopist. Oximetry will be used throughout the procedure. During endoscopy, up to 10 mL of duodenal aspirate will be collected with clean tubing. Using the same tubing, 20 mL 0.9% of sterile saline will be used to collect duodenal lavage. A brushing will be collected using an endoscopic cytology brush, and then the brush will be cut off into 1000 μL PBS. For histology, 3 biopsies will be collected into normal saline using 2.8 mm biopsy forceps, orientated on cellulose acetate paper (Sartorius, Gottingen, Germany) in the endoscopy room and placed in formalin thereafter. An additional 5 biopsies will be collected into 3 cryovials (2+2+1). All samples collected during endoscopy, except for the 3 histology biopsies, will be snap-frozen in liquid nitrogen immediately after collection. At the end of day 3, the participant will be given urine and stool collection devices for the next day.

### Day 4

Only stool and urine samples will be collected.

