## Methods

### Study outcomes

The expected outcomes for each aim are shown in
Table 1.

**Table 1. T1:** Summary of outcomes with reference to study aims.

	Measured outcome	Detail
*Aim 1*	*Protein digestion and absorption using stable isotope tracers*	Assessment of ^13^C spirulina digestion (global index by breath ^13^CO _2_) and absorption using ^13^C Phe (from spirulina) and ^2^H labelled free Phe administered orally.
	*Bidirectional transmucosal amino acid flux (BTAAF)*	A novel tool involving dual infusion of differentially labelled amino acid tracers (Phe/Leu) orally and intravenously for the assessment of EE severity.
*Aim 2*	*Fluorescein*	A novel non-invasive measure of intestinal permeability using orally dosed fluorescein and a finger probe (transcutaneous fluorescence spectroscopy) for detection of systemically circulating fluorescein.
*Aim 3*	*Microbiome analysis*	I. Faecal species abundance and diversity indexes by 16s rRNA sequencing. II. In country deep metagenomic sequencing by long read (Nanopore) sequencing compared with other short-read platforms (Illumina). III. Evaluation of microbial communities in EE and their ability to uptake intestinal amino acids, including conversion of L-amino acids to D-forms.
	*Metabolic phenotyping*	I. Untargeted metabolomics ( ^1^H-NMR) of plasma, urine and faecal water. II. Targeted quantification (MS) of intestinal, plasma and urine amino acids (unlabelled + labelled) before and after administration of oral and intravenous stable isotopes.
	*Metaproteomic analysis*	1) Proteomic analysis of intestinal biopsies for expression of key mucosal proteins in biopsies (mucins and tight junction proteins including Zonulin, claudins and occludins). * 2) Dynamic proteomic analysis of key target proteins to assess mucosal and tight junction protein synthesis rates in biopsies by high-resolution MS and D2O labelling.
*Aim 4*	*Biomarker analysis*	Quantification of known markers of systemic inflammation, microbial translocation, and intestinal epithelial damage in plasma and stool.
	*Duodenal expression of PRR*	Profile the expression of bacterial, fungal, and viral PRR in the duodenal epithelium using immunohistochemistry.
	*Systemic immune cell analysis*	Characterisation of innate and adaptive systemic immune cell phenotypes using differential cell counting and flow cytometry.

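### Tracer doses differ between the Day 2/Day 3 text and Table 3: a probable 1000-fold unit misprint on Day 3, and an unresolved 57- to 143-fold conflict for free 2H8-Phe on Day 2

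*Protocol article*

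**What the plan says.** The doses appear twice in the article under Clinical investigations: Zambia, once in the Day 2 and Day 3 text and once in Table 3. Both texts refer to Table 3 for preparation, so they describe the same solutions.

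- **Day 3, intravenous bolus (Solution C).** The text has "5_-phenylalanine (0.6 mmol kg" per kg; Table 3 has "5_-Phe (0.6 μmol kg" per kg. The other Phe and Leu entries in Solutions C to F follow the same pattern.
- **Day 3, filter.** The sentence on the bolus describes "normal saline filtered through a 0.2 mm syringe filter".
- **Day 3, arginine tracer.** The text and Solution E agree: "1.667 mg L-arginine-(guanidineimino".
- **Day 2, free 2H8-Phe (Solution A).** The text has "8_)-Phe (0.035 mg kg" per kg; Table 3 has "8_)-Phe (200 mg) in 200 mL water".
- **Day 2, spirulina.** The text and Solution A agree: "C-spirulina protein (1.25 mg kg" per kg.
- **Day 2, deuterated water.** The text gives 1 g per kg; Table 3 gives 1 mL per kg.

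Table 1, under Aim 1, assesses absorption from the 13C-Phe released by spirulina together with 2H "labelled free Phe administered orally".

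**The concern.** Two statements of one dose cannot both be right, and these are doses given to participants.

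On Day 3 the stake is safety of the printed text: an intravenous bolus stands at 1000 times the dose in the preparation table. The intended figure can be inferred, but a dosing sentence should not need inference.

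On Day 2 the stake is the Aim 1 measurement. Free 2H8-Phe and 13C-spirulina are given in the same drink and both enter the absorption assessment. If both are dosed per kg, their proportion is the same in everyone. If the free Phe is a flat 200 mg and spirulina is per kg, the proportion changes with body weight. Weight may also differ between Misisi residents and the high socio-economic controls, although the article gives no weights. Aims and objectives lists dosing among the things the protocol is meant to determine, so the printed dose is not incidental.

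**Working it through.** **Inputs.** Doses are from the Day 2 text, the Day 3 text and Table 3. Assumed, because the article does not give them: body weights of 40, 60 and 100 kg; molar masses of 170.2 (2H5-Phe), 134.2 (2H3-Leu) and about 173.2 g/mol (2H8-Phe); D2O density 1.107 g/mL.

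**1. Day 3, the eight entries side by side**

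| Solution | Tracer | Text (mmol/kg) | Table 3 (μmol/kg) |
|---|---|---|---|
| C, IV bolus | 2H5-Phe | 0.6 | 0.6 |
| C, IV bolus | 2H3-Leu | 1.2 | 1.2 |
| D, IV infusion | 2H5-Phe | 0.15 | 0.15 |
| D, IV infusion | 2H3-Leu | 0.3 | 0.3 |
| E, oral bolus | 13C6-Phe | 0.6 | 0.6 |
| E, oral bolus | 13C6-Leu | 1.2 | 1.2 |
| F, oral sips | 13C6-Phe | 0.15 | 0.15 |
| F, oral sips | 13C6-Leu | 0.3 | 0.3 |

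All eight differ by exactly 1000. Reading mmol as μmol makes all eight agree.

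**2. Is the mmol reading plausible?** Mass in Solution C = dose × weight × molar mass. At 60 kg:

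- Phe: 0.6 × 60 × 170.2 = 6,127 mg = 6.13 g
- Leu: 1.2 × 60 × 134.2 = 9,662 mg = 9.66 g
- Total: 15.79 g in 10 mL of saline

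The totals are 10.53 g at 40 kg and 26.32 g at 100 kg. Read as μmol, the same totals are 10.53, 15.79 and 26.32 mg. Grams of amino acid in 10 mL is not credible. The 0.2 mm filter printed with the bolus shows the same substitution of m for μ.

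**3. Day 2, free 2H8-Phe**

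| Weight | Text: 0.035 × weight | Table 3 | Ratio |
|---|---|---|---|
| 40 kg | 1.4 mg | 200 mg | 200/1.4 = 143 |
| 60 kg | 2.1 mg | 200 mg | 200/2.1 = 95 |
| 100 kg | 3.5 mg | 200 mg | 200/3.5 = 57 |

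**4. Can a slip reconcile them?**

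- As 0.035 g/kg: 1,400 to 3,500 mg over 40 to 100 kg, which is 7 to 17.5 times 200 mg.
- As 0.035 mmol/kg: 0.035 × 40 × 173.2 = 242 mg and 0.035 × 100 × 173.2 = 606 mg, which is 1.2 to 3.0 times 200 mg.
- As μg: the gap widens 1000-fold.
- As a decimal slip, 3.5 mg/kg: equals 200 mg only at 200/3.5 = 57 kg.

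None reproduces 200 mg across the weight range, and each leaves open whether the dose is per kg or flat.

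**5. Proportion of free Phe to spirulina by mass.** Spirulina at 1.25 mg/kg is 50, 75 and 125 mg at 40, 60 and 100 kg.

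- By the text: 0.035/1.25 = 0.028 at every weight.
- By Table 3: 200/50 = 4.0, 200/75 = 2.7, 200/125 = 1.6, a spread of 4.0/1.6 = 2.5-fold.

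**6. Deuterated water (minor).** 1 mL weighs 1.107 g, so 1 mL/kg is about 11% more than 1 g/kg.

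**The case against.** The Day 3 discrepancy largely resolves itself. The numerals match, the literal reading is implausible, the filter size shows the same misprint, and the text defers to Table 3. A Greek letter lost in typesetting or file conversion is a possible cause. The μ survives elsewhere in the text, including the brush volume on Day 3 and the section thickness under Histology and immunohistochemistry analysis, so a blanket conversion fault is not shown. This part stands: it is a probable misprint with no effect on any analysis, and the gram totals only show why the mmol reading should be rejected.

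The Day 2 text carries the same pointer to Table 3, so one could argue that 200 mg governs there too. That is fair as far as it goes, but it does not settle the matter. The sentence with the pointer also states a different amount on a different basis, and unlike Day 3 nothing else in the article shows which figure is the slip.

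Finally, nowhere does the article require a constant proportion of free Phe to spirulina. With known doses, each response can be expressed relative to its own tracer dose, as the sample size section does for the sucrose breath test. The ratio in step 5 is also free Phe to whole spirulina protein, not labelled Phe to labelled Phe. So bias in Aim 1 is not shown. What remains is that expressing results relative to dose requires knowing the dose, and the article prints two.

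**Conclusion.** The concern holds. All eight Day 3 Phe/Leu doses are 1000-fold apart between text and Table 3, almost certainly through μ printed as m, with Table 3 correct. The Day 2 2H8-Phe dose is a true contradiction in both amount and basis, 57- to 143-fold over an assumed 100 to 40 kg, and the article does not resolve it. The fold range rests on the assumed weights; the difference between per-kg and flat dosing does not. The deuterated water units are a minor mismatch of about 11% on an assumed density. No sample size, power or error-rate figure is affected, and nothing here shows that any participant received a wrong dose. It should be fixed because these are administered doses, one of them an intravenous bolus, and the Day 2 tracer feeds Aim 1.

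**What to change.** 1. In the Day 3 text, change mmol to μmol for all eight Phe/Leu doses and give the filter pore size as 0.2 μm, after confirming both against the approved protocol.
2. State one 2H8-Phe dose and one basis, per kg or flat, in both the Day 2 text and Table 3, checked against the approved protocol and the preparation records.
3. State that the Aim 1 analysis uses the 2H8-Phe and spirulina doses actually dispensed to each participant.
4. Give deuterated water in one unit throughout.

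The cost is a text correction and a check of existing records. No participants or procedures are added.

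### Day 3 intravenous tracer: volume, rate and duration in Table 3 and the text do not agree, and blood sampling is 4 h in the text but 3 h in Figure 2, so the tracer input and the status of the late samples are undefined

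*Protocol article*

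**What the plan says.** All the statements are in the protocol article, under the Zambian clinical investigations.

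- **Table 3, solution D:** labelled phenylalanine and leucine, "made up to 20 mL in sterile filtered normal saline", with the administration entry "Day 3, given intravenously as continuous infusion over 3 hours".
- **Day 3 text, infusion:** "solution D) will be commenced, at 5 mL h"⁻¹. No duration is given there.
- **Day 3 text, blood:** "2 mL every 20 mins for the first 1 h and every 30 mins for the remaining 3 h, and 5mL for the last sample". Breath follows the same pattern: "Breath samples will be collected every 20 mins for the first 1 h and every 30 mins for the remaining 3 h".
- **Figure 2 caption, Day 3 blood:** "intermediate 2 mL heparinised blood samples every 20 mins for 1 h and every 30 mins for the last 2 h".
- **Day 3 text, endoscopy:** "After 240 mins (4 h) the participant will be transferred to the endoscopy room". The duodenal aspirate is taken there.

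Table 1 lists BTAAF under Aim 1 as a novel tool that rests on giving differently labelled Phe and Leu by mouth and by vein.

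**The concern.** Volume, rate and duration are tied together: any two fix the third. Here all three are printed and they do not fit. The sampling window, which should be planned around the infusion, is printed in two lengths.

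Two quantities that matter to a dual-tracer measurement are therefore unclear. One is how much intravenous tracer enters per hour. The other is when it stops, which decides whether the last blood samples are taken with the tracer still running or after it has ended. BTAAF compares the fate of intravenous and oral labels, so an estimator that uses the input rate, or that takes late samples as taken during infusion, could be affected. If staff resolved the conflict differently on different days, some of the variation between participants would come from procedure and not from enteropathy.

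**Working it through.** **Inputs.** Volume 20 mL and duration 3 h (Table 3, solution D); rate 5 mL/h (Day 3 text); Phe 0.15 and Leu 0.3 μmol/kg (Table 3). The Day 3 text prints these amounts in millimoles. That is a separate matter and does not affect the ratios below. The start of the infusion is taken as time zero.

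**1. The plan's own duration.** Duration = volume / rate = 20 / 5 = 4.0 h. The stated 3 h is not reproduced.

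**2. What each pair of figures implies.** Hourly Phe input is calculated on the assumption that 0.15 μmol/kg is the total contained in 20 mL, since no time unit is printed.

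| Figures kept | Third figure | Phe input (μmol/kg/h) | End |
|---|---|---|---|
| 20 mL and 5 mL/h | 4.0 h | 0.15 × 5/20 = 0.0375 | 240 min |
| 5 mL/h and 3 h | 15 mL (15/20 = 75%) | 0.15 × 5/20 = 0.0375 | 180 min |
| 20 mL and 3 h | 20/3 = 6.67 mL/h | 0.15/3 = 0.050 | 180 min |

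The ratio of the two inputs is 0.050 / 0.0375 = 1.33. For Leu the figures are 0.100 and 0.075, with the same ratio. The 75% and the 1.33 are one 3:4 ratio seen from two sides, not two separate effects.

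**3. Blood sampling times after the dose.**

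- Day 3 text (1 h + 3 h): 20, 40, 60, 90, 120, 150, 180, 210, 240 min. Nine times.
- Figure 2 caption (1 h + 2 h): 20, 40, 60, 90, 120, 150, 180 min. Seven times.

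**4. Bloods against the end of infusion.**

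| Infusion end | Day 3 text schedule | Figure 2 schedule |
|---|---|---|
| 180 min | 2 of 9 after the end (210 min by 30 min, 240 min by 60 min) | none after the end |
| 240 min | none after the end | none after the end |

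**5. Aspirate.** It follows 240 min, so it comes at least 60 min after a 3-h end. After a 4-h end it still comes later, but the gap is 60 min shorter.

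**6. How far a sample after the end could differ.** The documents give no tracer kinetics. Assuming simple exponential decline with a half-life anywhere from 15 to 120 min, the intravenous tracer left 60 min after stopping is 0.5^(60/15) = 6% to 0.5^(60/120) = 71% of its value at the stop. The range is too wide to support any single figure for the effect.

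**The case against.** The preparation volume need not equal the infused volume. If 5 mL is overage, 15 mL over 3 h at 5 mL/h is coherent. This is a fair reading, but the article does not state it. It also leaves the 3-h and 4-h sampling windows in conflict, and on the text schedule it puts the 210- and 240-min bloods after the infusion.

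It can also be said that volume, rate, 4 h of blood and breath sampling and endoscopy after 240 min all fit a 4-h infusion, so that all nine bloods fall within it. That is true, but Table 3 and the Figure 2 caption then need correcting, and the documents do not settle which entries are in error.

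A reader might go further and infer that the flux estimate is biased, that its dose term is wrong for every participant, or that it is overstated by a third. The article does not support this. It gives no BTAAF estimator, no steady-state assumption and no list of the samples that enter. The one-third figure needs the total-dose reading, an estimator proportional to input, and an analyst who uses the nominal 3-h rate and not the pump setting. Even then, an error common to all participants would leave ranks and correlations with morphometry unchanged, and comparison with morphometry is what the statistical analysis plan section sets out.

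Nor is the timing of the aspirate caused by the mismatch, since it follows the infusion on either reading. A condensed article may also leave the estimator and recording details to a fuller document; their absence is not the criticism here. The conflict between printed figures remains.

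**Conclusion.** The contradictions stand on the text alone: 20 mL at 5 mL/h is 4 h against a stated 3 h, and blood sampling is 4 h in one place and 3 h in another. Confidence in that arithmetic is high.

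The consequence is conditional. The intravenous input rate, its end time and the status of two of the nine text-scheduled bloods are undefined, which could bias BTAAF. The 1.33-fold difference in input holds only if the Table 3 amounts are totals in 20 mL, and it carries into BTAAF only if the estimator is proportional to input. For the aspirate, the conflict changes only the length of its gap after the infusion ends. Because these figures set the tracer supply and sampling for a named Aim 1 outcome, they should be corrected and not passed over as clerical.

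**What to change.** Reconcile the volume, rate and duration of solution D and the blood sampling window across Table 3, the Day 3 text and the Figure 2 caption. If part of the 20 mL is overage, say so. The investigators must decide which figures are right; this review does not propose a schedule.

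In the analysis, compute BTAAF from the tracer rate actually delivered and the actual infusion start and stop times, not from the nominal 3-h figure. Late bloods can then be classed as taken during or after the infusion.

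The cost is a text correction and, if not already captured, a few recorded fields (pump rate, start and stop times, volume delivered). No procedure is added. For participants already studied, pump or nursing records should be checked, since delivery details that were never recorded may not be recoverable.
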